### Control Group

The control group will receive standard survivorship care delivered through telehealth. All sites have a standard survivorship visit that includes the use of a software package to generate the delivery of a paper SCP based on American Society of Clinical Oncology guidelines. This comprises a treatment summary, an upcoming surveillance visit schedule, and guidance on late effects. This visit includes the delivery of information and specifically does not include goal setting, use of the dual framework technique (described in the “Intervention” section), acceptance and commitment intervention (described in the “Intervention” section), self-management coaching, or the use of motivational interviewing techniques. To ensure fidelity to control group standards, all visits will be audio-recorded and reviewed to evaluate for evidence of contamination of the control condition. Telephone-based booster contacts will serve as attention control with structured delivery of educational material on surveillance visits and bone health.

### Intervention

POSTCare is a structured cancer survivorship navigation platform that seeks to improve cancer outcomes for survivors. Key elements of the platform include personalized self-management support and tailored SCP delivery. The platform is delivered through telehealth (a video platform) and comprises an initial survivorship care transition visit that includes the development and delivery of a personalized care plan. Within the platform framework, a trained nurse uses motivational interviewing and communication skills to engage patients in the development of a POSTCare plan that incorporates health goals and strategies related to surveillance, symptom management, and health behavior [34,35]. Survivor engagement with the POSTCare plan is supported by monthly navigator phone booster follow-up for 2 months, also delivered by the nurse survivorship navigator. Participants will be offered an additional nonstructured phone check-in before their first follow-up visit at 3 months.

### Patient-Centered Design

The POSTCare session begins with the coach engaging the survivor in sharing her cancer treatment narrative, anchoring the activity to the patient’s experience and needs. The identification of health goals is the central activity of POSTCare and distinguishes this approach to survivorship care from those that simply deliver information. The survivor is asked to think about identifying 1 or more goals in the following survivorship domains: social support, healthy habits, symptom management, and coping with uncertainty. Resource and activity support materials related to goals are maintained in the POSTCare-O web-based survivorship toolkit and used by coaches. As an adaptation for the needs of survivors of ovarian cancer, the dual framework [31] is introduced by coaches in goal-setting as a strategy for living with uncertainty. The dual framework is a strategy used in palliative encounters to help patients focus on what living well means to them while holding the possibility of advancing illness or death in the same cognitive frame. It provides a structure to anchor the focus on living well across the longitudinal trajectory of survivorship navigation. We will introduce a brief cognitive exercise derived from acceptance and commitment therapy to address recurrence worry if participants articulate this as a survivorship concern and goal [22,36-38]. Our informants indicated that using a focus on what it means to live well despite serious illness is an acceptable palliative intervention even at the initiation of the survivorship period when they wish to be focused on the positive aspects of treatment completion.

The coach and survivor strategize about potential barriers to goal accomplishment and explore ways to address barriers, with the coach using motivational interviewing techniques to explore survivor ambiguity about health goals and nurture self-efficacy in working toward goals. The components of the platform, drawn from an evidence-based approach to care setting transition [24,25,27,39-41], include an emphasis on survivor engagement and activation. The average length of the coaching session is 75 minutes, which includes the creation of the SCP [21].

Booster survivorship navigation telephone contacts occur at 4 weeks and 8 weeks after baseline. The survivorship coaches will review health goals, including living well, adjust goals as needed, discuss progress, identify barriers, and brainstorm about strategies to overcome barriers. The survivorship coaching intervention is delivered through telehealth by the nurse survivorship navigation coach. For participants who do not have a smart device, the intervention can be delivered through a smart device provided by the study in a clinic setting.

### Qualitative Methods

Qualitative methods will be used to inform the adaptation and refinement of the intervention. Interviews will be undertaken with 3 groups of informants: women living with ovarian cancer; nurses who have been trained in the POSTCare model; and gynecologic oncologists, clinic staff, and administrators. Semistructured exit interviews will be conducted by specially trained research team members within 30 days of completing the intervention. Although the exit interview questions will be stated as broad questions, the researcher will be trained to probe for details, including asking for specifics and operational examples.

We will partner with women enrolled in this study to conduct semistructured interviews on the POSTCare survivorship care experience. Interview topics will include (1) timing of survivorship care—both initiation of survivorship transition and longitudinal care; (2) critique of proposed intervention content and existing materials; (3) understanding the meaning of this intervention for participants; (4) exploring individual differences between experiences and outcomes; and (5) evaluation of intervention length, intensity, frequency, and mode of delivery. Interviews will be conducted with gynecologic oncology nurses who have completed the POSTCare-O web-based training and used components of the POSTCare model to provide the intervention. Finally, we will explore the same interview topics with clinic staff at each study site to learn what elements of the POSTCare model work well in their clinical setting, which elements they are able to use routinely, which components seem to most meet the needs of their patients, and which elements of survivorship care they find most satisfying.

### Outcome Measures

We will use the FACT-O instrument as the primary end point for the clinical trial. The FACT-O is a 38-item assessment that comprises a core QOL instrument (the FACT-General) and a 12-item ovarian module. The internal consistency for the complete instrument is Cronbach α=.92, and the test-retest reliability is *r*=0.81 [42]. The subscales demonstrate similar acceptable psychometrics. This instrument is widely used in trials and will allow us to meaningfully compare the results of this trial to those of other studies that examine QOL. The minimally important difference is the “smallest difference” in FACT-O scores that patients perceive as clinically important and is 3-8 points [43]. We have powered the study to identify this level of change.

The Patient Health Questionnaire-9 (PHQ-9) is a widely used screening tool for depression, consisting of 9 items [44]. It takes approximately 5 minutes to complete and has been found to be a valid and reliable measure of depressive symptoms in various populations, including patients with cancer. The total score on the PHQ-9 can range from 9 to 27, with higher scores indicating a higher level of depressive symptom burden. A study by Thekkumpurath et al [45] found that the PHQ-9 was a valid and reliable measure of depression in patients with cancer and recommended its use in clinical practice. Additionally, the PHQ-9 has been used as an outcome measure in various interventions for depression, including those targeting patients with cancer [46]. The PHQ-9 has demonstrated good internal consistency and test-retest reliability, with a coefficient α=.89 and an intraclass correlation coefficient of 0.84, respectively [44].

The Fear of Cancer Recurrence-7 (FCR-7) is a 7-item questionnaire designed to offer a psychometrically sound assessment of fear of cancer recurrence with a limited response burden. The instrument comprises 7 questions: 5 that use a 5-point Likert scale ranging from 1 (not at all) to 5 (all the time), and a single question that uses an 11-point Likert scale ranging from 0 (not at all) to 10 (a great deal). Total scores on the measure range from 6 to 45 [47]. A cutoff score of 17 or above reflects moderate fear of cancer recurrence, and a score of 27 or above indicates severe fear of cancer recurrence. The measure demonstrates good internal consistency (Cronbach α=.92) and validity as compared to measures of anxiety and depression [48].

Other measures used as secondary outcomes and potential predictors were selected with a priority on acceptable psychometric performance in similar populations and acceptable performance in one of our previous studies.

“Aim 1” proposes to implement a RCT devised to compare QOL measures among patients with ovarian cancer randomized to receive usual care versus the POSTCare survivorship care transition program. Outcome measures, including the FACT-O QOL survey, the FCR-7 survey, and the PHQ-9, will be collected at baseline as well as 12 and 24 weeks after the initial course of adjuvant chemotherapy. The primary end point will consist of the 12-week FACT-O survey. The sample size of 120 patients provides at least 80% power to detect a 7% increase in the mean FACT-O score for women randomized to the POSTCare survivorship care intervention. This is sufficient to ascertain a minimally important difference of 8 points. Secondary outcomes (Table 1) will also be assessed at 12 and 24 weeks. Baseline descriptive statistics will be presented by site. Longitudinal analysis of the FACT-O QOL scores will use a mixed effects linear model with a restricted maximum likelihood estimation method, and an unstructured covariance matrix will be used to estimate trends. An interaction between intervention and time will be estimated to explore the effectiveness of POSTCare for time-varying trends [49]. Though the mixed effect model can accommodate some degree of missing data under the ignorability assumption, we also plan to use multiple imputations using the random forest method [50,51] to accommodate missing data (if greater than 10% of survey items), which will be assumed to be missing at random. In the event of a sign of a violation of that assumption, a pattern mixture model will be used to mitigate the effect of informative missingness. Secondary analyses will evaluate relationships between baseline and 12-week FACT-O scores and clinical end points progression-free survival (PFS) and overall survival (OS). Cox proportional hazard models will be used to estimate the relative risk of PFS and death per increase in FACT-O [52]. Ties in failure times will be handled with the approximate likelihood of Efron. PFS and OS will be measured from the date of randomization. PFS is defined as the minimum amount of time until clinical progression, death, or the date of last contact. OS is the duration from randomization to death or to the date of last contact (right-censoring). As is customary, secondary analyses are not powered but may help generate additional evidence that needs to be tested in the future by a properly powered study.

**Table 1 table1:** Summary of variables and outcomes.

Variables for outcome analysis			Measures	Reliability, *r*	Source

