## Methods

### Study Design

We will conduct a 2-arm RCT to evaluate the impact of a telehealth-delivered survivorship transition care platform. Survivors of ovarian cancer (N=120) will be randomly allocated to receive survivorship care either using the POSTCare Platform or standard of care. Study design and reporting will be in accordance with the CONSORT (Consolidated Standards of Reporting Trials) checklist. We will use quantitative and qualitative methodologies in a concurrent triangulation mixed methods design using qualitative data to augment our interpretation of quantitative data. Outcomes will be collected at baseline, 12 weeks, and 24 weeks, with the primary outcome being a QOL assessment at 12 weeks after the survivorship transition (Figures 2 and 3).

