### Recruitment Procedures

Study research coordinators will have access to the electronic medical record at each site. They will collaborate with clinical personnel to identify patients who will be completing initial therapy. Coordinators will work to identify patients in treatment at least 8 weeks before the completion of therapy. They will identify an upcoming clinical appointment, either in clinic or infusion, where the team will approach patients to provide information about the study, answer questions they may have, and obtain informed consent. Enrolled participants will be asked to complete a web-based, self-administered survey using a smart device to collect baseline measurements before randomization.

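### The PFS model on 12-week FACT-O starts its clock at randomization, so progressions before the survey count as events predicted by a later score

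*Protocol article*

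**What the plan says.** All the relevant text is in the Outcome Measures section of the protocol article, under Aim 1.

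- Covariates and endpoints: "Secondary analyses will evaluate relationships between baseline and 12-week FACT-O scores and clinical end points progression-free survival (PFS) and overall survival (OS").
- Model: "Cox proportional hazard models will be used to estimate the relative risk of PFS and death per increase in FACT-O".
- Time origin, given once for both endpoints and both scores: "PFS and OS will be measured from the date of randomization".
- PFS: "PFS is defined as the minimum amount of time until clinical progression, death, or the date of last contact".
- OS: "OS is the duration from randomization to death or to the date of last contact (right-censoring").

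The baseline survey is done "to collect baseline measurements before randomization" (Recruitment Procedures). The 12-week score comes later, but its anchor varies. In Outcome Measures the surveys "will be collected at baseline as well as 12 and 24 weeks after the initial course of adjuvant chemotherapy", while Study Design describes the trial "with the primary outcome being a QOL assessment at 12 weeks after the survivorship transition".

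The section gives no separate rule for the 12-week score and does not say what happens to women who progress before that survey. It calls the secondary analyses unpowered and meant to generate evidence for a later, properly powered study.

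**The concern.** A Cox model with time zero at randomization compares, at each event time, the covariate of the woman who has the event with the covariates of those still at risk. That is sound only if the covariate was known by then. The baseline score meets this condition. The 12-week score does not meet it for any progression between randomization and the survey.

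Take a woman who progresses at week 6 and fills in the survey at week 12. Her event is recorded at week 6 and explained by a score that may already reflect the progression. A consequence of progression is then read as a predictor of it, and a larger sample does not remove the error.

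At stake is the credibility of the QOL-PFS association. These analyses are meant to inform a future study, and a false association would misdirect it.

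**Working it through.** **No figure to reproduce.** The document gives no event count, hazard ratio or power for the survival analyses. The size below therefore depends on stated assumptions.

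**Inputs**

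- N = 120 (Study Design).
- FACT-O SD is not given. The stated 80% power for 8 points with 60 per arm implies, at an assumed two-sided alpha of 0.05, SD = 8 / [(1.960 + 0.842) × √(2/60)] = 15.6. Runs used 15.6 or 16.
- Median PFS is not given. The Introduction places most recurrences at 18-24 months after chemotherapy. This is taken as an assumed median of 18-24 months, with 12 months as a pessimistic case.
- The FACT-O drop after progression is not given. Assumed 0 to 16 points; the document's minimally important difference is 3-8 points.
- Censoring is assumed uniform over 6-24 months.

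**Step 1: how many events precede the survey.** Twelve weeks is 84 / 30.4375 = 2.76 months. With a constant hazard and median m months, P = 1 − 2^(−2.76/m), and the events by 24 months (ignoring censoring) are 120 × (1 − 2^(−24/m)).

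| Median PFS | P(progression before week 12) | Of 120 | Events by 24 months | Share |
|---|---|---|---|---|
| 12 months | 14.7% | 17.7 | 90.0 | 19.6% |
| 18 months | 10.1% | 12.1 | 72.4 | 16.7% |
| 24 months | 7.7% | 9.2 | 60.0 | 15.3% |

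**Step 2: bias under a constant hazard.** FACT-O has no true effect, every early progressor completes the survey, and there are 3,000 runs per cell. Each cell gives the hazard ratio per 8 points and the type I error at a nominal 5%.

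| Median, drop | Clock from randomization | 12-week landmark |
|---|---|---|
| 18 months, 0 | 0.998, 5.5% | 0.999, 5.3% |
| 18 months, 4 | 0.968, 6.6% | 0.997, 5.0% |
| 18 months, 8 | 0.942, 13.4% | 1.001, 5.4% |
| 18 months, 16 | 0.886, 39.7% | 0.999, 4.5% |
| 24 months, 0 | 1.001, 5.0% | 1.001, 5.0% |
| 24 months, 4 | 0.974, 6.2% | 1.001, 4.7% |
| 24 months, 8 | 0.946, 10.3% | 1.003, 5.2% |
| 24 months, 16 | 0.890, 31.1% | 0.998, 4.8% |

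The extreme corner, a 12-month median with a 16-point drop, gives 0.883 and about 50%.

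**Step 3: a rising hazard.** The Introduction says that women usually finish initial treatment without evidence of disease, which suggests a low early hazard. With a Weibull of shape k, P = 1 − 2^(−(2.76/m)^k). For m = 18, k = 1.5 gives 4.1% (about 5 women) and k = 2 gives 1.6% (about 2 women). With a 12-point drop, the hazard ratio and type I error are 0.96 and 9% for k = 1.5, and 0.98 and 7% for k = 2. Over medians of 18-24 months and drops of 8-16 points, the results are about 0.95-0.98 and 6-12%.

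**Step 4: incomplete surveys.** Under a constant hazard with an 18-month median and a 12-point drop, type I error is about 25% with full completion. It is about 10-11% if half of the early progressors have no 12-week score.

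**The case against.** The strongest reply is that measuring PFS from randomization is not wrong in itself. It suits the baseline score, and it is compatible with delayed entry or a time-dependent FACT-O. On this view only a risk-set rule for one exploratory model is missing, which an analysis plan could supply. This stands in part: the time origin need not change if one of those devices is used. But the text fixes the covariate, the model and a single origin, with nothing to separate the two scores. Its plain reading is a fixed 12-week covariate from day 0, and that reading is biased.

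The second reply concerns size, and it stands. The large figures need a constant hazard, a big drop and full survey completion. The 50% corner also needs a median below the 18-24 months in the Introduction and a drop twice the upper end of the minimally important difference. Health changes are a listed reason for dropout, so some early progressors will have no score. The two anchors for the 12-week survey leave its distance from randomization uncertain, which alters the size but does not remove the flaw.

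A reader might infer more than the document supports:

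- **That the OS hazard ratio is biased too.** A woman who dies before the survey has no score. Among those with one, a common shift of the clock leaves the risk sets, and so the hazard ratio, unchanged. Only Cox relative risks are planned.
- **That scores would be imputed after death.** Multiple imputation is described alongside the longitudinal FACT-O analysis. Nothing carries imputed scores into the Cox models.
- **That last contact counts as a PFS event.** The PFS sentence does not call it censoring, but the adjoining OS sentence does, and the intent is clear.

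**Conclusion.** The point holds for one model: PFS on the 12-week FACT-O score. As written, progressions before the survey enter as events explained by a later measurement, and the association leans towards higher QOL with longer PFS if progression lowers FACT-O.

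The direction is clear; the size is not. It runs from no bias (no drop in FACT-O), through a modest effect (0.95-0.98 per 8 points, 6-12% false positives, if the early hazard is low), to a serious one (down to 0.88 and about 50%, in the least favourable constant-hazard case). The Introduction's account of recurrence timing fits the modest range better. All of these rest on an assumed PFS distribution, drop, SD and censoring pattern.

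The baseline-score models, the primary endpoint, the sample size and the comparison of arms are untouched. That the analysis is secondary and unpowered limits the consequence but does not excuse a bias that is easily avoided.

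**What to change.** Keep randomization as time zero for the baseline FACT-O models. For the 12-week score, do one of the following and say so:

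- start follow-up at the actual 12-week survey date, among women alive and progression-free on that date for PFS (alive, for OS); or
- keep the origin at randomization and enter FACT-O as a time-dependent covariate that takes its 12-week value only from the survey date.

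Using the actual survey date also avoids dependence on which anchor defines week 12.

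The cost is a sentence of wording and a small change in code, with no new data. The landmark model loses the events before the survey: about 9-12 of 120 women under a constant hazard with an 18-24 month median, and fewer if the early hazard is low. Those events cannot validly inform a model of a score measured after them. In the simulations the landmark brought the null hazard ratio to about 1.00 and the type I error to 4.5-5.4%.

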**Primary outcomes**					
		Quality of Life	Functional Assessment of Cancer Therapy-Ovarian [42]	.92	Patient self-report
		Depression	Patient Health Questionnaire-9 [45]	.94	Patient self-report
		Recurrence anxiety	Fear of Cancer Recurrence-7 [47]	.93	Patient self-report
**Secondary outcomes**					
		Patient self-efficacy	Stanford Chronic Illness Self-Efficacy Scale [53] Patient Activation Measure [54]	.91 .87-.91	Patient self-report
		Satisfaction with communication	Stanford communication with physicians [55]	.89	Patient self-report
		Health care use	Stanford Health Care Utilization [53]	.76-.97	Patient self-report
		Satisfaction with care coordination	Stanford Self Efficacy [55]	.91	Patient self-report
		Perception of Informational Support	Patient-Reported Outcomes Measurement Information System: informational support measure [56]	—^a^	Patient self-report
		Symptom Burden	MD Anderson Symptom Inventory for ovarian cancer Stanford Social/Role Activities Limitations	.89-.90 .91	Patient self-report
**Predictor variables**					
	Demographic or medical information		Demographic questionnaire: will include gender, race, and treatment history	N/A^b^	Electronic medical record
	Cancer coping style		Brief version of the Coping Orientation to Problems Experienced [57]	.75	Patient self-report
	Social support		Social Provisions Scale [58]	.92	Patient self-report
	Education level		Stanford Education [59]	N/A	Patient self-report

^a^Not available.

^b^N/A: not applicable.

“Aim 2” applies mediation analysis to the data acquired from the RCT proposed in Aim 1. Aim 2 explores the potential for heterogeneity in the effectiveness of the POSTCare survivorship program. The primary end point for aim 2 is QOL at 6 months, as measured by the FACT-O. Combining both study arms, subgroup analysis will assess the distributions of potential prognostic factors for QOL at 6 months. Analyses will adjust for statistically significant prognostic factors. Mediation modeling will be applied to decompose the relationships among the care plans, intermediate surrogate markers of QOL acquired during the course of follow-up, and QOL at 6 months. Surrogate markers include patient activation, goal setting, self-efficacy, and care satisfaction, to be collected at 12 weeks and 24 weeks from surveys identified in Table 1. For each surrogate marker, an intermediate response will be defined. The direct and indirect impact of POSTCare will be estimated for each surrogate response using mediation analysis [60-62] to elucidate the causal mechanisms of QOL and assist with planning for larger confirmatory studies and studies in other disease types.

Qualitative data for intervention adaptation will be analyzed using a thematic analysis framework. At the outset of the process of analysis and interpretation, the qualitative team will read each transcript from interviews in its entirety to achieve a global sense of substance and context. Working independently of one another, we will engage in a line-by-line search for recurring ideas, coding each transcript for themes. After identifying dominant themes, we will evaluate the degree of consensus among participants. An initial codebook will be developed from the interview guide and adaptation framework. A master code book will be entered into NVivo (version 11; QSR International). The data will be merged with the quantitative data to inform interpretation and draw stronger inferences. As described by Farquhar et al [63], mixed methods are particularly beneficial where the interventions are complex and the platform for evaluation and identification of suitable outcomes is challenging. Insights gained from quantitative and qualitative approaches complement each other to provide a more in-depth understanding. This deeper understanding can inform the process of refining interventions and hypothesis generation and facilitate replication of the intervention through greater knowledge of the active components and potential barriers to implementation. Moreover, qualitative research can be used to examine and address key uncertainties before dissemination efforts [64]. Interviews will be conducted by experienced qualitative interviewers on our established research team. We anticipate conducting up to 30 interviews at the outset of the process of analysis and interpretation*.* We will use all data sources to inform the revision of the POSTCare-O platform before active dissemination [65-68].

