**Objective:**

The overall goal of this study is to test processes of care that support quality of life (QOL) in survivorship. The specific aims are threefold: first, to test the efficacy of the POSTCare platform in supporting QOL, reducing depressive symptom burden, and reducing recurrence worry. In our second aim, we will examine factors that mediate the effect of the intervention. Our final aim focuses on understanding aspects of care platform design and delivery that may affect the potential for dissemination.

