**Figure 1 figure1:**
[figure not shown]
Alignment of POSTCare elements with the chronic care model. Developed by The ACT Center, formerly known as the MacColl Center for Health Care Innovation, reprinted with permission from ACP-ASIM Journals and Book.

In POSTCare-O, the POSTCare platform is adapted to meet the needs of survivors of ovarian cancer. We worked with members of the CanSurvive GYN Cancer Support Group in Birmingham, Alabama, and gynecologic oncologists to identify survivorship priorities and needs. Patients with ovarian cancer and their caregivers were clear that they wanted to focus on living well during the survivorship transition, and clinicians felt that concerns that may be important for other cancer types, such as transition to primary care, might be of lesser priority in the context of ovarian cancer. They helped us understand that the essential “work” of cancer survivorship in ovarian cancer is the work of living well despite serious illness and the specter of mortality. Using the palliative dual framework, a technique used to assist patients in the task of living well despite serious illness [30,31], and a brief acceptance and commitment therapy intervention [22], we have incorporated a goal focused on living well with a serious illness that was not a component of the breast cancer POSTCare platform.

The overarching goal of this study is to test processes of care that support outcomes, including QOL, in survivorship. We will use QOL as a primary outcome, but we will also look at factors such as recurrence worry, depressive symptom burden, and survivorship efficacy that may also be influenced by improved care processes. The specific aims of this study are to conduct a randomized controlled trial (RCT) enrolling 120 women with advanced ovarian cancer. We will test the efficacy of the POSTCare platform in supporting QOL, reducing depressive symptom burden, and reducing recurrence worry. In our second aim, we will examine factors associated with the impact of the intervention. Our final aim focuses on understanding aspects of care platform design and delivery that are likely to affect the potential for dissemination. We will use both qualitative and quantitative methods to assess patient experience, provider experience, and pragmatic aspects of clinical implementation, with the goal of redesigning the implementation for greater dissemination potential.

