Although overt efforts have been made to minimize limitations by design, this study will have several limitations. While we expect to meet our sample size target of recruiting 120 women with ovarian cancer, practical aspects of participant recruitment and budgetary constraints will constrain our ability to stratify the population and evaluate potential mediators. Furthermore, the highly structured nature of care delivery for this study, including consistent intervention delivery by a single research nurse, may not reflect the conditions encountered in a “real-world” implementation of this health services intervention that is intended to be optimized for dissemination. While we have put in place measures to address concerns related to intervention fidelity, including review of recordings of intervention sessions with fidelity checklists and ongoing education to ensure consistent delivery, inconsistent delivery remains a potential source of bias for this study. This study will take place at 2 US “safety net” clinics that serve economically disadvantaged patients primarily, as well as a university practice that serves individuals with private or federal insurance. While this design should give us a representative sample within our geographic region, the results may not be generalizable to other regions of the United States or health care systems outside the United States. Despite these limitations, this study will make a significant contribution to survivorship science in ovarian cancer by examining aspects of supportive care that may improve QOL for patients.

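### Aim 2 claims to explore heterogeneity in POSTCare's effect, but none of the analyses it names compares that effect across baseline factors; its mediation component is not affected

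*Protocol article*

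**What the plan says.** The Aim 2 paragraph follows Table 1 in the Outcome Measures section of the protocol article. It introduces mediation analysis and then states a second purpose: "Aim 2 explores the potential for heterogeneity in the effectiveness of the POSTCare survivorship program". The endpoint is FACT-O at 6 months. Three analyses are named:

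- A subgroup step: "Combining both study arms, subgroup analysis will assess the distributions of potential prognostic factors for QOL at 6 months".
- Use of its result: "Analyses will adjust for statistically significant prognostic factors".
- Mediation through patient activation, goal setting, self-efficacy and care satisfaction: "The direct and indirect impact of POSTCare will be estimated for each surrogate response using mediation analysis".

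The article names one interaction, under Aim 1 in Outcome Measures: "An interaction between intervention and time will be estimated to explore the effectiveness of POSTCare for time-varying trends". It involves time, not a baseline characteristic.

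Aim 2 is described differently elsewhere. The Objective in the Abstract says "In our second aim, we will examine factors that mediate the effect of the intervention". The end of the Introduction says "In our second aim, we will examine factors associated with the impact of the intervention". The limitations in the Discussion concede that "budgetary constraints will constrain our ability to stratify the population and evaluate potential mediators".

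**The concern.** Heterogeneity of effectiveness means that the difference between POSTCare and control varies with some characteristic of the woman at baseline. To study it, that difference has to be compared across levels of the characteristic. The three named analyses do other things:

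- Combining the arms and relating factors to 6-month quality of life gives prognostic associations.
- Entering those factors as main effects assumes one common POSTCare effect at every level of each factor.
- Mediation asks how an effect arises through variables measured after randomization, not in whom it is larger.

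A stated part of Aim 2 would therefore go unanswered. The article says Aim 2 should help plan larger confirmatory studies and studies in other cancers, so the distinction between prognosis and benefit matters for what follows.

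A linked weakness is that covariates are chosen by significance in the same 120 women. This makes the adjustment set depend on the data, and in a sample of this size a relevant covariate can miss the threshold by chance.

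**Working it through.** **The plan's own figure.** No figure is given for Aim 2. The only power statement is Aim 1's: N=120 (60 per arm), at least 80% power, a 7% increase in mean FACT-O, and a difference of 8 points. The article gives no SD and no alpha. Assuming two-sided 0.05, the largest SD that gives 80% power is

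8 / [(1.960 + 0.842) × √(2/60)] = 8 / (2.802 × 0.1826) ≈ 15.6.

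The Aim 1 figure is attainable but cannot be verified. It serves here only as a source for a working SD.

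**What each analysis estimates.** Take a 50:50 baseline factor X, arm A (0 or 1), and mean outcome = a·A + b·X + c·A·X.

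- Pooled-arm difference between levels of X: b + c/2.
- POSTCare effect adjusted for X as a main effect: a + c/2.
- Heterogeneity: c.

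Neither of the first two isolates c.

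**Simulation.** 4,000 trials per scenario, 60 per arm, SD 15.64, critical value 1.98:

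| Scenario | a, b, c | Pooled difference b + c/2 | Adjusted effect a + c/2 | Pooled test flags X | Interaction test flags X |
|---|---|---|---|---|---|
| Prognostic only, effect of 8 in everyone | 8, 8, 0 | 8 | 8 | 77% | 5% |
| Effect 0 vs 16, no control-arm association | 0, 0, 16 | 8 | 8 | 77% | 79% |
| Effect 0 vs 16, pooled means equal | 0, −8, 16 | 0 | 8 | 3% | 79% |

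The first two rows look the same to the pooled test and to the adjusted effect, although only the second contains heterogeneity. In the third row the pooled screen passes over a true modifier, but only because the pooled subgroup means were set equal.

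**Precision of an interaction at this sample size.** Assumed SD 15.5, no dropout, 30 women per cell:

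- SE of the main effect = 15.5 × √(2/60) = 2.83.
- SE of the interaction = 15.5 × √(4/30) = 5.66, twice the main-effect SE.
- 95% half-width = 1.98 × 5.66 = 11.2 points.

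The half-width is 1.98 × √(4/30) × SD = 0.723 × SD, which gives 8.7 points at SD 12, 14.5 at SD 20 and 18.1 at SD 25.

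Power for an 8-point interaction, at SD 15.64: SE = 15.64 × √(4/30) = 5.71; 8/5.71 − 1.96 = −0.56; Φ(−0.56) ≈ 0.29. Power of 80% needs an interaction of (1.960 + 0.842) × 5.71 ≈ 16 points, or for 8 points about 120 × (16/8)² = 480 women.

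**The case against.** The strongest reply is that Aim 2 is a mediation aim containing one loose sentence. The Abstract's Objective describes it as mediation, its Results section speaks of identifying mediators, and the Aim 2 paragraph both opens and closes on mediation. This stands: mediation is the main content, and the mismatch does not touch it.

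The pooled step also has a proper use. Randomization does not remove confounding between mediator and outcome, so covariates prognostic for 6-month quality of life belong in the mediation models. That stands too, and interaction terms would not do that job.

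A reader might infer two harms that the document does not support:

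- *That prognostic factors will be reported as marking women who benefit.* The article calls them prognostic and uses them only for adjustment.
- *That the significance screen will generally discard effect modifiers.* This happens only when pooled subgroup means happen to be similar. In the plain 0-versus-16 scenario the screen flags the factor in 77% of trials.

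It can also be said that a fuller protocol or analysis plan may contain interaction terms, that the aim is worded as exploratory, and that the limitations already concede restricted scope for stratifying. The point does not rest on a missing list of moderators. The article states a question and attaches to it analyses that address a different one. Nor can the combined-arms sentence readily be read as one model with an interaction: it speaks of factors prognostic for quality of life, and the next sentence uses them only for adjustment. Calling the aim exploratory lowers the stakes but does not reconcile the two.

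**Conclusion.** The point holds in a limited form. The heterogeneity sentence and the named analyses do not match, so that part of Aim 2 cannot be answered as written. A reader might go further and conclude that Aim 2 as a whole fails, or that the pooled step should be abandoned. Neither follows: the mediation work does not depend on the heterogeneity question, and prognostic covariates are needed for it. The primary 12-week comparison is untouched.

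The conclusion about the mismatch rests on the text and needs no assumed number. The sizes do rest on assumptions: an SD of about 15.5 back-calculated from the Aim 1 power statement and carried over to 6 months, two-sided 0.05, all 120 women assessed, and a 50:50 factor. Under these, an interaction could be estimated to within about ±11 points, wider than the 8-point target, with about 29% power for an 8-point difference in effect. Dropout, an unbalanced factor or more than two levels would widen this. Any heterogeneity analysis here can only be exploratory.

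**What to change.** 1. **Heterogeneity: choose one.** Either add arm-by-factor interaction terms to the FACT-O model for a very short list of baseline factors named in advance, reporting each estimate with its 95% confidence interval as exploratory; or delete the heterogeneity sentence and describe Aim 2 as mediation only. The Introduction's wording of Aim 2 should then agree with the choice.
2. **Covariates.** Keep prognostic covariates in the mediation models, but replace selection by significance with a set fixed in advance that includes baseline FACT-O and the stratification factors.
3. **Labelling.** Describe any pooled-arm result as prognostic.

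The cost is a change of wording and, under the first option, a few extra models on data the trial already plans to collect. The downside is wide intervals, which the report must present as such. Deleting the sentence costs nothing in analysis but gives up the heterogeneity question.
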